## 8.4 Interim and Unscheduled Visits

Additional visits may occur in either phase of the study as needed for complications, participant/parent/LAR concerns or to assess wound healing that is delayed beyond 42 days. Participants and their parents/LAR as appropriate will be told they should come for an unscheduled visit if they experience medical events such as: difficulty urinating, increasing swelling with discoloration of the penis, signs of infection (purulence), severe or increasing pain, or other significant concern. Participants and their parents/LAR as appropriate will also be asked to return to the clinic if they experience any untoward symptoms from the ring or any problems while wearing the ring that causes them significant concern. At interim or unscheduled visits, the following tasks, activities or documents will be completed:

| Day of Visit               | Study procedures to be conducted                                                                                                                                                                                                                                                                                                                                          |
|----------------------------|---------------------------------------------------------------------------------------------------------------------------------------------------------------------------------------------------------------------------------------------------------------------------------------------------------------------------------------------------------------------------|
| Interim/ Unscheduled visit | 
 
1. Conduct genital examination
 
2. Examine penis and assess wound healing;
 
3. Review AEs and SAEs, if applicable;
 
4. Review concomitant medications, if applicable;
 
5. Take penile photographs if participant agrees;
 
6. Schedule additional follow-up visits if necessary.
 
 |

## 8.5 Summary of Activities at each Study Visit

### Phase I

| STUDY ACTIVITY                                                              | Day 0 Visit | Day 7 visit | Day 14, 21,
28, 35, 42 Visits | Final Visit |
|-----------------------------------------------------------------------------|-------------|-------------|----------------------------------|-------------|
| Informed Consent Process                                                    | X           |             |                                  |             |
| Assign Participant Number                                                   | X           |             |                                  |             |
| Physical Exam and Medical History                                           | X           |             |                                  |             |
| Genital Exam                                                                | X           | X           | X                                | X           |
| Screening Checklist                                                         | X           |             |                                  |             |
| Demographic Survey                                                          | X           |             |                                  |             |
| Obtain Locator Information                                                  | X           |             |                                  |             |
| Circumcision Procedure                                                      | X           |             |                                  |             |
| Shang Ring Device Removal (for those randomized to the 7 day removal group) |             | X           |                                  |             |
| Assess Pain and/or AEs or SAEs                                              | X           | X           | X                                | X           |
| If permitted take Penile Photograph                                         | X           | X           | X                                | X           |
| Review Concomitant Medications                                              | X           | X           | X                                | X           |
| Schedule follow-up if wound not healed                                      | X           | X           | X                                |             |
| Reimburse Participant                                                       |             | X           | X                                | X           |
| Final Status Form                                                           |             |             |                                  | X           |

### Phase II

| STUDY ACTIVITY                         | Day 0 Visit | Day 7 Visit | Day 42 Visit |
|----------------------------------------|-------------|-------------|--------------|
| Informed Consent Process               | X           |             |              |
| Assign Participant Number              | X           |             |              |
| Physical Exam and Medical History      | X           |             |              |
| Genital Exam                           | X           | X           | X            |
| Screening Checklist                    | X           |             |              |
| Demographic Survey                     | X           |             |              |
| Obtain Locator Information             | X           |             |              |
| Randomization                          | X           |             |              |
| Circumcision Procedure                 | X           |             |              |
| Shang Ring Device Removal              |             | X           |              |
| Assess Pain and/or AEs or SAEs         | X           | X           | X            |
| If permitted take Penile Photograph    | X           | X           | X            |
| Review Concomitant Medications         | X           | X           | X            |
| Schedule Follow-Up Visit               | X           | X           |              |
| Schedule follow-up if wound not healed |             |             | X            |
| Reimburse Participant                  |             | X           | X            |
| Final Status Form                      |             |             | X            |

## 8.6 Participant Compensation

Participants or their parents/LAR will be given a small cash stipend to cover transport cost to and from the study site for the scheduled follow-up visits. This will not include the first (day 0) circumcision day visit. The amount of the stipend will be 350 Kenyan Shillings (KES), the same amount we have used in our previous Shang Ring studies in Homa Bay. Stipends will not be disbursed for unscheduled/interim visits other than those scheduled due to delayed healing beyond 42 days. As is the case with circumcisions provided as part of the national VMMC program, the circumcision procedure and follow-up care will be provided at no cost.

## 9.0 STATISTICAL CONSIDERATIONS

### 9.1 Study Size Justification

By recruiting 230 participants into Phase I of the study we expect to have complete follow-up data on at least 200. This sample size number is in line with the recommendations from the World Health Organization for clinical evaluation of MC devices, which is based on an ability to rule out an AE rate of about 5% with a new use of a device that has already been shown to be safe in a larger group of men in RCTs and demonstration studies. (WHO 2012)

In Phase II, by recruiting 345 participants, we expect to have complete follow-up data on at least 300. For comparing postoperative pain scores, we will randomize 345 males in 2:1 ratio to topical vs. injectable anesthesia for circumcision. This sample would provide 100% power to detect a mean difference of 1 on the 0 to 10 pain scale using a 2-sided test at the 0.05 significance level. This calculation assumes a standard deviation of 1.8, which is based on prior data. For other binary endpoints, this sample size will provide at least 80% power to detect absolute differences in proportions between groups of at least 20% separately within each site using two-sided tests at the 0.05 significance level. We will not make any adjustments for multiple comparisons between randomized groups.

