4. Most men (94.7%) were very satisfied with the appearance of their circumcised penis. Almost all men (99.8%) would recommend circumcision to a friend or family member and 98.8% would specifically recommend a Shang Ring circumcision
5. Of the 21 providers, 19 (90.5%) preferred the Shang Ring over conventional surgery

The Shang Ring has a good safety profile in routine service delivery settings and is preferred by most clients and providers, making it a good option for scaling up adult VMMC in Africa.

Most recently, we completed a pilot study of use of the Shang Ring in children in Kenya. This was the first use of the device in children of all ages, including infants, outside of China. A study of the Shang Ring in adolescent boys 16-17 years old is ongoing in Uganda. Published studies from China found the Shang Ring easy and simple to use with shorter procedure times, fewer complications and better cosmetic results compared to conventional MC techniques for children (Yan et al., 2010; Pan et al., 2013). In our pilot study in Kenya, a total of 80 boys from four age groups were enrolled: <1 (n=6), 1-5 (n=30), 6-12 (n=23), and 13-17 (n=21) years old. Participants were circumcised using the Shang Ring no-flip technique and rings were removed 5-7 days post-circumcision. Results showed that:

1. Circumcision and device removal times were quick (mean circumcision and device removal times  $7.5 \pm 3.1$  and  $4.5 \pm 2.2$  minutes, respectively)
2. There were no severe AEs. Four moderate AEs were noted and were managed successfully with conservative management
3. Mean healing time was  $29.9 \pm 7.3$  days

4. Most patients or their parents/guardians (94.7%) were very satisfied with cosmesis and would recommend Shang Ring circumcision to others (95.0%)

The results of this pilot study suggest that the Shang Ring for male circumcision in boys is safe, effective and acceptable. Larger prospective trials are required to further validate the use of the Shang Ring in the pediatric population. In the most recent pilot study, we successfully used the no-flip technique in 30 boys between the ages of 10 and 17 years, the first use of this technique outside of China. In the study described in this protocol, we will study the no-flip technique in a larger sample of men and boys 10 years of age and older.

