## 3.0 ENDPOINTS

### 3.1 Phase I

#### 3.1.1 Primary Endpoints

- We will address the primary objective by evaluating the rate of moderate and severe adverse eventsi (AEs) following Shang Ring MC using the no-flip technique based on clinical exam findings. Other safety endpoints will include documentation of time to complete clinical wound healing,ii device-related malfunctions and occurrences of device displacement.

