## 4.0 STUDY DESIGN

The study, to be conducted in two phases, will examine procedural and clinical outcomes, as well as participant and provider acceptability, of adaptations of the Shang Ring technique for male circumcision that would simplify its use and increase its acceptability.

- Phase I will be non-comparative for exploration of the no-flip technique for Shang Ring circumcision (i.e. all participants will be circumcised using the no-flip Shang Ring technique). Historical data from standard Shang Ring circumcisions conducted in Africa (Kenya, Uganda and Zambia) will be used as the comparison group. Men will be randomized to removal at 7 days after circumcision vs. delayed removal, to assess occurrence and safety of spontaneous detachments following circumcision with the no-flip technique.
- Phase II will compare the use of topical vs. injectable anesthesia for Shang Ring circumcision. Participants will be randomized to topical vs. injectable anesthesia in a 2:1 ratio. We rationalize the 2:1 randomization scheme given that we will have just completed Phase I in which 200 men and boys will have been circumcised using the no-flip technique with injected anesthesia. However, given the subjectivity associated with using reported pain as the primary endpoint, we believe it is critical to randomize participants in this phase of the study.

Because of the possibility that boys and men could have different outcomes after no-flip Shang Ring circumcision or could respond differently to use of topical anesthesia, we

will recruit participants equally in two age groups in both phases; 50% of participants recruited in each phase will be between 10-15 years old and the other 50% over 15 years old. Because recruitment shall be taking place at two sites, which may have different recruitment rates, and because clients need to be randomized 1:1 and 2:1 into the Phase 1 and Phase 2 treatment groups, respectively, appropriate stratified block randomization techniques by age will be applied to achieve the intended number of participants per treatment group.

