## 6.0 STUDY PARTICIPANTS

### 6.1 Population Base

Participants will be recruited for the study from boys and men, 10 years and older who are seeking MC at one of the study sites. A total of 575 participants shall be enrolled into the study (230 in Phase I and 345 in Phase II). Because of the possibility that boys and men could 1) have different outcomes following no-flip Shang Ring circumcision or 2) respond differently to use of topical anesthesia, we will recruit participants in two age groups, with half of the participants in each phase being 10-15 years old and the other half being over 15 years of age.

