| Mild AEs                                                                                                  | 43     | 2.2% (1.6%, 2.9%) |
| Anesthetic complication                                                                                   | 1      |                   |
| Pain during placement                                                                                     | 13     |                   |
| Edema                                                                                                     | 3      |                   |
| Injury                                                                                                    | 3      |                   |
| Partial detachment                                                                                        | 3      |                   |
| Bleeding                                                                                                  | 2      |                   |
| Wound disruption                                                                                          | 15     |                   |
| Insufficient skin removed                                                                                 | 3      |                   |

Adapted from WHO Technical Advisory Group on Innovations in Male Circumcision: Evaluation of Two Adult Devices. Meeting report: Published in August 2013. Geneva, Switzerland. ISBN 978 92 4 150563 5.

The figures in the above table are for Shang Ring circumcision in adults. In a study in China which involved 824 children the complication included infection (0.4%), edema (3.2%), and insufficient skin removal (0.9%). Average time for wound healing was 13.4 ± 5.8 days after circumcision (Yan, 2010). We found low rates AEs in our recently completed study of use of the Shang Ring in children in Kenya; among the 80 boys under 18 years of age who participated in the study there were no severe AEs and four moderate AEs (three cases of wound disruption, all which healed with conservative management, as well as one case of postoperative pain requiring further analgesics).

During the follow up visits, study staff will assess and provide follow-up care and/or referrals for any post-operative complications. If complications or delayed healing require longer follow-up, men will be followed by study staff as long as necessary.

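### Phase I sets a pooled rate in boys and men against adult data with no age split, and its 5% rule-out holds well only if everyone has a rate near the adult 1%

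*Combined protocol and SAP*

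**What the plan says.** All references are to the combined protocol and SAP.

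- **Endpoint.** Section 3.1.1 addresses the Phase I primary objective by "evaluating the rate of moderate and severe adverse events" after no-flip circumcision.
- **Size.** Section 9.1: "By recruiting 230 participants into Phase I of the study we expect to have complete follow-up data on at least 200". That number is said to agree with a WHO recommendation "based on an ability to rule out an AE rate of about 5% with a new use of a device". No assumed true rate, interval method, sidedness, power or pass rule is given.
- **Age mix.** Section 4.0: "50% of participants recruited in each phase will be between 10-15 years old and the other 50% over 15 years old". The reason given there is that boys and men might not have the same outcomes. Section 6.1 repeats the split.
- **Comparison.** Section 4.0 calls Phase I non-comparative, but adds: "Historical data from standard Shang Ring circumcisions conducted in Africa (Kenya, Uganda and Zambia) will be used as the comparison group".
- **Adult results.** Table 2 in section 12.3.1 gives 20 moderate and no serious AEs in 1,983 placements. The text below it says: "The figures in the above table are for Shang Ring circumcision in adults".
- **Boys' results.** Section 1.3.2 reports the Kenyan pilot of 80 boys, all circumcised with no-flip. There were no severe AEs, and "Four moderate AEs were noted and were managed successfully with conservative management".
- **Analysis.** Section 9.2 tabulates Phase I AEs by severity, overall and by site. It lists no age split and no confidence interval for the Phase I rate. The 95% intervals it mentions are for differences between the Phase II anaesthesia groups.

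**The concern.** The design recognises age as a possible modifier of outcome, recruits and randomises by it, and then leaves it out of the planned safety summary. The comparison data supplied cover only one of the two age groups.

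Two misreadings follow. If boys have more AEs than men whatever the technique, the pooled no-flip rate will exceed the adult rate, and this can be taken for an effect of no-flip. If the excess is confined to boys, pooling dilutes it. Section 4.0 also allows Phase II to open in one age group once Phase I recruitment there is complete and the safety evidence is judged sufficient. That decision can be age-specific, yet no age-specific AE table is planned.

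The size argument in 9.1 rests on the device having been shown safe in a larger group of men. It does not say what happens to the 5% property if the younger half has a different rate.

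**Working it through.** **Inputs**
- n = 200 evaluable (230 recruited) and a threshold of about 5%: section 9.1.
- About 100 per age group: section 4.0.
- Adult rate 20/1,983 = 1.0%: Table 2. Table 2 lists moderate and serious AEs, so 1.0% is taken as the adult moderate/severe rate.
- Boys' rate 4/80 = 5.0%: sections 1.3.2 and 12.3.1. The exact 95% CI is 1.4% to 12.3% (computed).
- Assumption: ruling out 5% means that the upper limit of an exact 95% interval lies below 5%. The documents do not say this, so one-sided limits are shown too.

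**Step 1: how many events are allowed.** The exact upper limit for x events in n is the 0.975 quantile of Beta(x+1, n-x), or the 0.95 quantile if one-sided.
- n=200, two-sided: 3 events 4.32%, 4 events 5.04%. At most 3 are allowed.
- n=200, one-sided: 4 events 4.52%, 5 events 5.18%. At most 4 are allowed.
- n=230, two-sided: 5 events, limit just under 5.00%; 6 events 5.59%. At most 5 are allowed, by the narrowest margin.

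**Step 2: the plan's own claim, one common rate.** No power is stated, so there is no figure to reproduce. The chance of excluding 5% is P(X ≤ k) for X ~ Bin(200, p):

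| True rate | Two-sided (≤3) | One-sided (≤4) |
|---|---|---|
| 1% | 86% | 95% |
| 2% | 43% | 63% |
| 3% | 15% | 28% |

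If everyone has the adult rate, 200 is adequate.

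**Step 3: a mix of rates.** Let A ~ Bin(100, 20/1,983) for those over 15 and B ~ Bin(100, 0.05) for those aged 10-15. The expected count is 1.0 + 5.0 = 6.0, or 3.0% pooled. The chance is the sum over i = 0 to k of P(A=i) × P(B ≤ k-i):
- two-sided, n=200: 14.5%
- one-sided, n=200: 27.8%
- two-sided, 115 + 115 analysed: 30.7%
- older group at 2.0% instead (the field-study AE rate in section 1.3.2), n=200: 7.7% two-sided, 16.7% one-sided

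**Step 4: uncertainty in the boys' rate** (older group at 1.0%, n=200, two-sided):

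| Boys' rate | Chance of excluding 5% |
|---|---|
| 1.4% | 78% |
| 2% | 65% |
| 3% | 43% |
| 5% | 15% |
| 12.3% | about nil |

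**Step 5: each age group alone (n=100).** Two-sided, 0 events gives an upper limit of 3.62% and 1 event gives 5.45%. Only a zero count excludes 5%; even at a true 1% that happens 37% of the time. One-sided, 1 event is allowed (4.66%), a 74% chance at 1%.

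**Step 6: age against technique.** In the step 3 mix the pooled expectation is three times the adult 1.0%. The documents cannot divide that between age and technique: the adult results offered as the comparison are standard-technique, and the only African boys' series is no-flip.

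**The case against.** **The boys' 5.0% is a weak anchor.** This stands. The 80 boys were under 1 (6), 1-5 (30), 6-12 (23) and 13-17 (21) years old; only 30 were aged 10-17, and the four AEs are not split by age. It is not a rate for ages 10-15, so the 15% is one point in a range. A reader might also take 15% as the chance at the boys' rate. It is not: at 5% in all 200 the chance is 0.9%. The 15% needs the half-and-half mix, n=200 and a two-sided limit.

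**The 5% is attributed, not a decision rule.** This stands. Section 9.1 reports the basis of a recommendation and sets no criterion. A reader might infer that Phase I will probably fail, but there is nothing to fail. Four events are turned away only because 5.04% exceeds a threshold described as approximate.

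**No final test against the historical data is planned.** This also stands. A reader might infer that a significant excess over 20/1,983 is likely even if no-flip is harmless, but the Phase I analysis in 9.2 is descriptive. The interim guideline in 9.3 that permits stopping concerns severe AEs, of which the boys' series had none.

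**A detailed analysis plan is to follow, and section 4.0 involves the DSMB before Phase II opens by age group.** This answers only in part. The later plan could add age strata, but nothing in 9.2 commits it to do so.

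**Conclusion.** The point holds as a gap in reporting and justification. A primary safety rate is pooled over two groups that the protocol says may differ, and the comparison results supplied cover adults only. Age and technique are therefore confounded, and a higher rate in boys could be hidden.

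The 5% statement is well supported only when everyone is near the adult 1%: 86% with a two-sided limit, 95% with a one-sided limit. Under the illustrative 5%/1% mix it falls to about 15% (two-sided, n=200), 28% (one-sided) or 31% (two-sided, 230 analysed). Over the boys' interval it runs from 78% to about nil (two-sided, n=200). All of this assumes exact limits and a threshold applied to moderate/severe AEs, which 9.1 does not spell out.

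The documents do not support saying that the trial will miss a target, that a false alarm is likely, or that the true rate at ages 10-15 is 5%. Because Phase I is descriptive and has no pass rule, this should be fixed, but it does not undermine the phase.

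**What to change.** **Section 9.2**
- Report the moderate/severe AE proportion with an exact 95% CI separately for ages 10-15 and over 15, beside the overall and by-site figures.
- Compare only participants aged 18 and over with the adult historical data. The older stratum also takes in ages 16-17, so record how many are 18 or over; the documents give no figure.
- State that no standard-technique control is described for boys, and show the 80-boy series as context only.

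**Section 9.1**
- State the interval, its sidedness and the AE category to which the 5% refers.
- Give the chance of excluding 5% at n=200 for true rates of 1%, 2% and 3%: 86%, 43% and 15% two-sided (3 or fewer events); 95%, 63% and 28% one-sided (4 or fewer).

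**Cost.** Some wording and a few table columns, with no change to recruitment. The rule-out statement becomes weaker, the intervals per age group are wider (with 100 per group, a single event already has a two-sided upper limit of 5.45%), and the historical comparison uses fewer participants.

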## 5.0 STUDY SITES

This study will be conducted at two primary sites in Kenya: (1) Homa Bay County Hospital, Homa Bay County, in the western region, and (2) Vipingo Health Center, in Kilifi County, along the coast. The study sites were determined in conjunction with NASCOP VMMC National coordinator and county health authorities. Circumcisions will be done by trained medical officers, clinical officers or nurses.

Staff at the Homa Bay County Hospital have had extensive experience with use of the Shang Ring in adults, having been the site where the previous four Shang Ring studies with adults described earlier were conducted. They also have experience with Shang Ring circumcisions in boys under 18 years old as the county hospital was the site for the Shang Ring in children pilot study described above.

Staff from the site in Vipingo conduct conventional surgical circumcisions in men and boys but do not currently have experience with the Shang Ring. Clinical officers and nurses from the site will be trained on the Shang Ring procedures by staff from Homa Bay prior to study enrollment. The staff from Homa Bay have experience training other male circumcision providers on use of the Shang Ring, having previously trained providers from other facilities in Kenya, as well as from Uganda and Zambia.

Due to the volume of men that we plan to recruit in a relatively short time period, each primary site may use outreach services or additional clinics to recruit and circumcise study participants similar to what we did in the Shang Ring Demonstration Study conducted in 2012 in Homa Bay (KEMRI NON-SSC protocol # 299) where we involved five satellite sites and incorporated outreach activities within Homa Bay district.

The priority sub-counties for additional recruitment within Homa Bay County will be selected with guidance from County Health Management Team. This will similarly be how priority sub-counties would be selected around our Vipingo site. Previously, within Homa Bay county, Ndiru and Nyangoro Health Centres participated in the Demonstration Study and still have staff that were previously trained on Shang Ring VMMC technique.

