All other endpoints will be summarized by anesthetic technique and compared between groups using either two-sample t-tests or chi-squared tests, as appropriate for the endpoint, all conducted at the two-sided 0.05 significance level. We will not make any adjustments for multiple comparisons. 95% confidence intervals for differences between groups will be presented. Missing data will be assumed to be missing in random fashion and ignored.

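### Section 9.1 claims at least 80% power within each site for any 20-point difference in proportions; its own sample size gives about 66% to 71% in the worst case

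*Combined protocol and SAP*

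**What the plan says.** Section 9.1 (Study Size Justification) sets the Phase II size: "we will randomize 345 males in 2:1 ratio to topical vs. injectable anesthesia", of whom "we expect to have complete follow-up data on at least 300". After a power statement for pain, it turns to the other, binary endpoints and claims "at least 80% power to detect absolute differences in proportions between groups of at least 20% separately within each site". The error rate is 5%, two-sided. The section gives no baseline proportion and no division of the sample between sites.

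Three other places bear on the claim:

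- Section 5.0: "This study will be conducted at two primary sites in Kenya".
- Section 4.0: "Because recruitment shall be taking place at two sites, which may have different recruitment rates" is given as one reason for stratified block randomization.
- Section 9.2: endpoints other than pain and adverse events are to be "compared between groups using either two-sample t-tests or chi-squared tests", without adjustment for multiplicity.

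**The concern.** The power for a given difference in proportions depends on where the proportions lie. A guarantee of at least 80% with no baseline stated must therefore hold in the middle of the range, where the variance is largest. Dividing 300 or 345 participants first by site and then 2:1 by arm leaves about 50 to 57 in the smaller arm, which looks too few for a 20-point difference there.

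What is at stake is how site-level results are read. A reader who trusts section 9.1 would take a non-significant comparison at one site as reasonable evidence against a 20-point difference. If true power is nearer two in three, that reading is not justified.

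**Working it through.** **Inputs from the documents.** Two-sided 0.05; 345 randomized 2:1 (230 vs 115); at least 300 complete (200 vs 100); two sites; chi-squared test.

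**Assumption.** The division between sites is not stated. I take it as equal, the most favourable case for a claim about each site:

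- 300 complete: 150 per site, 100 vs 50.
- All 345 analysed: about 172 per site, 115 vs 57.

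**Check on the neighbouring figure.** The pain statement uses a difference of 1 and SD 1.8. Power is Φ(1/[1.8·√(1/n₁+1/n₂)] − 1.96).

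- 230 vs 115: Φ(4.86 − 1.96) = 99.8%.
- 200 vs 100: Φ(4.54 − 1.96) = 99.5%.

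The stated 100% is therefore right to rounding.

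**Within-site power, by formula.** With p̄ the pooled proportion and d the difference:

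- SE₀ = √[p̄(1−p̄)(1/n₁+1/n₂)]
- SE₁ = √[p₁(1−p₁)/n₁ + p₂(1−p₂)/n₂]
- power = Φ[(d − 1.96·SE₀)/SE₁]

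For 50 at 40% and 100 at 60%: p̄ = (20+60)/150 = 0.533; SE₀ = √(0.2489 × 0.03) = 0.0864; SE₁ = √(0.24/50 + 0.24/100) = 0.0849. Power = Φ[(0.20 − 0.1694)/0.0849] = Φ(0.361) = 64.1%.

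**Within-site power, exact.** Summing the binomial probabilities of every outcome that the uncorrected chi-squared test rejects gives the table below. A range shows the two directions of the difference.

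| Proportions | 100 vs 50 (300 complete) | 115 vs 57 (all 345) |
|---|---|---|
| 5% vs 25% | 92–94% | 95–96% |
| 10% vs 30% | 83–86% | 88–90% |
| 20% vs 40% | 71–74% | 77–79% |
| 30% vs 50% | 67% | 71–72% |
| 40% vs 60% | 66.2% | 70.7% |

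By symmetry the same values hold at the upper end (75% vs 95%, and so on). The minimum over all baselines is 66.1% for 100 vs 50 and 70.7% for 115 vs 57.

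**Where 80% is reached.** With 100 vs 50, the lower proportion must be no more than about 12% (injectable arm lower) or 14% (injectable arm higher). With 115 vs 57 the limits are about 16% and 19%.

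**What would be needed.** At 40% vs 60%, 80% power needs 146 vs 73, which is 219 per site and 438 over two sites, against 345 planned. With the planned numbers, the worst-case difference detectable with 80% power is about 24 points (300) or 22.5 points (345).

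**Variants tried, all at 40% vs 60%.**

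- Unequal sites, for example 60:40 with 300 complete (my illustration): the smaller site has 80 vs 40 and 54% power.
- 1:1 allocation, exact: 75 vs 75 gives 70.6% and 86 vs 86 gives 76.8%. The 2:1 ratio costs only about 4 to 6 points; splitting by site is the main cause.
- Yates correction: 57% with 100 vs 50, and 63% with 115 vs 57.
- One-sided 0.05 with all 345 (80.3%), or 100 per arm per site at 1:1 (81.2%): these reach 80% but contradict the stated inputs.
- Pooled over sites: 91.4% (200 vs 100) or 94.4% (230 vs 115), each the worst case over baselines.

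**The case against.** The strongest reply is that the claim holds where the protocol has data. Adverse-event rates in its earlier studies run from about 1% to 7.6% (sections 1.3.2 and 12.3.1). In the field study, 94.7% were very satisfied with appearance, and about 91% were healed at 35 to 42 days. At 5% vs 25% or 75% vs 95%, a site of 100 vs 50 has 92% to 94% power; at 8% vs 28% it has 87% to 89%. This stands, and a sentence limited to such endpoints would be correct. But section 9.1 sets no such limit, and other Phase II endpoints, such as problems during anaesthesia and satisfaction with the anaesthetic, have no baseline in the documents.

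Second, 345 may be the fairer number for outcomes recorded on the day of the procedure, when later loss to follow-up does not apply. That is reasonable, but it moves the worst case only to about 71%.

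Third, the equal split is assumed, and section 4.0 says only that recruitment rates may differ. That is true. Unequal recruitment would help the larger site and hurt the smaller, so the claim for each site still fails.

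Fourth, these are secondary endpoints. Section 9.2 plans site-specific tabulation only for adverse events, with no within-site tests, and promises confidence intervals for differences between groups. This limits the practical harm. Enrolment, the primary analysis and the stopping guidelines do not depend on the sentence. The false assurance still stands in section 9.1.

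**Conclusion.** The statement is wrong as written. For a 20-point difference in mid-range proportions, power within a site is about 66% with the expected 300 completers and about 71% if all 345 are analysed (64% to 71% across the uncorrected two-sided calculations), not at least 80%. These figures assume equal sites; any other division lowers power at the smaller one, and none gives both sites the 219 they would need. The claim is true for proportions near 0 or 1, and for the comparison pooled over sites, where power is at least about 91%. This is an error in a power statement for secondary endpoints, and it leaves the Phase II pain comparison untouched.

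**What to change.** Replace the sentence in section 9.1. It should say:

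- Pooled over sites, 200 vs 100 completers give at least about 91% power for a 20-point difference in a binary endpoint (two-sided 0.05, chi-squared).
- Within a site of 100 vs 50, assuming equal recruitment, power for 20 points is about 66% in the worst case; 80% power is available for about 24 points.
- Power of 80% for 20 points within a site applies only when the lower proportion is at or below about 12%, or the higher at or above about 88%.
- If day-of-procedure endpoints will be analysed on all 345, the matching figures are about 71% and 22.5 points.

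State in sections 9.1 and 9.2 that site-specific comparisons are descriptive and will be reported with confidence intervals. No added enrolment is called for. The cost is a short text correction and a less favourable stated power.
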